### Recruitment

Participants will be recruited through advertisements in health centres, older daycare centres, senior centres and women’s centres in Murcia (Spain). In addition, publications with information about the trial will be made on social networks. All potential participants will be contacted personally by telephone before their inclusion in the study.

### Inclusion and exclusion procedures

To be included in the study, participants will have to meet the following criteria: will be male or female, aged 50 years or older, being physically independent, not having any pathology incompatible with the study, not having participated in a structured exercise programme for at least 1 year and signing the informed consent form. The exclusion criteria will be self-reported substance abuse or dependence disorder (alcohol, non-prescribed medications, etc), being under medical prescription for taking medications that could influence physical performance, suffering from any pathology contraindicated for the exercise programme or requiring specialised medical attention (infectious, renal, pulmonary, coronary diseases, etc), having low adherence during the programme or performing physical exercise outside the study. During the pre-test phase, health personnel will perform an ECG on each participant to corroborate their cardiac health just after signing the informed consent and before the assessment tests.

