### Randomisation and allocation

After baseline measurements, participants will be randomly assigned to the TG or CG. A research team member will create a randomisation sequence (1:1) before the trial begins. The investigators who will conduct the assessments are not aware of which group the participants belong to, and participants will be instructed not to disclose the group to which they had been assigned.

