### Control group

Individuals assigned to the CG (figure 1) will be instructed to continue their daily activities throughout the study. Participants’ habits and physical activity levels will be monitored over the 8-week study period using specific inquiries incorporated within the socio-demographic questionnaire.

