#### Adherence to the exercise programme

In the TG, each participant’s adherence to the exercise programme will be monitored. Adherence will be measured as the percentage of exercise sessions performed and/or the total number of scheduled sessions.

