## Statistical analysis

The qualitative variables will be summarised in frequency. In contrast, the quantitative variables will be summarised using mean and SD for the TG and CG across the assessment time points. To ensure rigorous statistical evaluation, special attention has been given to controlling the type I (alpha) error and Bonferroni’s correction will be used to achieve p=0.005 for statistical significance. To compare characteristics between and within groups, the principle of intention to treat will be applied, with adjustments made to adhere to the exercise programme. The following tests will be employed to assess baseline characteristic differences between the two groups: Student’s t-test for parametric numerical variables, Mann-Whitney test for non-parametric variables and χ^2^ test for categorical binary variables.

To compare changes within and between the TG and CG across baseline and follow-up assessments, the subsequent tests will be used: for variables exhibiting normal distribution, repeated measures analyses of variance. Given the multiple comparisons involved, post hoc analyses will be conducted using t-tests with Sidak corrections to control the type I error rate; for non-parametric variables, the Friedman test will be followed by the Wilcoxon test, and, to address the multiple comparisons, the Bonferroni correction will be applied.

SPSS V.25.0 statistical software will be used in all the analyses. A p value<0.05 will be used to determine significant differences; however, this will be adjusted appropriately in the presence of multiple comparisons, as detailed above.

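### Low adherence during the programme is an exclusion criterion, so randomised participants can be removed from the training arm only, which contradicts the stated intention to treat

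*Protocol article*

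**What the plan says.** Under Inclusion and exclusion procedures, the exclusion criteria end with "having low adherence during the programme or performing physical exercise outside the study". Exercise before the study has a separate inclusion criterion: "not having participated in a structured exercise programme for at least 1 year".

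Under Randomisation and allocation: "After baseline measurements, participants will be randomly assigned to the TG or CG". The 8-week programme follows.

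Under Adherence to the exercise programme: "In the TG, each participant’s adherence to the exercise programme will be monitored", and then "Adherence will be measured as the percentage of exercise sessions performed and/or the total number of scheduled sessions". Table 2 likewise schedules adherence in the training group's columns only.

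Under Control group, controls "will be instructed to continue their daily activities throughout the study". The same section adds: "Participants’ habits and physical activity levels will be monitored over the 8-week study period".

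Under Statistical analysis, for comparisons between and within groups, "the principle of intention to treat will be applied, with adjustments made to adhere to the exercise programme".

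**The concern.** An exclusion criterion normally acts before allocation. One that depends on behaviour during the programme cannot. It acts on people who have already been randomised, and here it can act on only one of the two arms. Training participants who attend poorly would leave the comparison, while the controls who would have attended poorly stay in. The two groups then differ in whatever goes with attendance (motivation, fitness, health), and the estimated effect mixes training with those characteristics.

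The article has no other stated analysis principle than intention to treat, and this criterion works against it. The question affects the between-group comparison for every outcome.

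**Working it through.** **Setting the sections side by side**

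1. Allocation comes after baseline and before the programme. Nobody can show low adherence to the programme at the time of allocation, so the criterion can remove only randomised people.
2. Adherence is recorded only in the training group, and controls are told to carry on as usual. The criterion therefore acts on one arm.
3. Intention to treat keeps all randomised participants in their allocated arm. Nothing in the article says that those excluded for low adherence stay in the analysis, or that the criterion only defines a per-protocol set. Items 1 to 3 cannot all hold together.
4. The outside-exercise item has no time qualifier. The existing one-year criterion and the 8-week monitoring of controls make use during the trial the natural reading, but the text does not settle it.
5. The definition of adherence joins two different quantities with and/or: a percentage of sessions performed, and a count of scheduled sessions. The second does not vary with attendance.

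**Illustrating the size**

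Inputs from the article: at least 60 per group, SD 4.2, significance levels 0.05 and 0.005. The article's 60 and its assumed error of 1.06 agree with each other as a 95% half-width for one mean: 1.96 × 4.2 / √60 = 1.063. The point here does not depend on that calculation; it only takes n and SD from it.

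Assumptions, not in the article: the true training effect is zero; a share q of the training group with the lowest adherence is removed; adherence follows a normal latent trait with correlation ρ to outcome change. The small loss of variance from truncation is ignored.

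- Bias in SD units = ρ × φ(z_q) / (1 − q). The factor φ(z_q)/(1 − q) is 0.195 at q = 10%, 0.350 at 20% and 0.497 at 30%.
- SE in SD units = √(1/[60(1 − q)] + 1/60).
- Type I error = P(|Z + bias/SE| > critical value), with critical value 1.96 at 0.05 and 2.807 at 0.005.

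Central case, q = 20% and ρ = 0.3: bias = 0.3 × 0.350 = 0.105 SD. SE = √(1/48 + 1/60) = 0.194. The ratio is 0.54. Type I error is 8.4% at 0.05 and 1.2% at 0.005.

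| q | ρ | Training group kept | Bias (SD) | SE | Type I at 0.05 | Type I at 0.005 |
|---|---|---|---|---|---|---|
| 10% | 0.1 | 54 | 0.02 | 0.188 | 5.1% | 0.5% |
| 20% | 0.3 | 48 | 0.105 | 0.194 | 8.4% | 1.2% |
| 30% | 0.5 | 42 | 0.25 | 0.201 | 23.5% | 5.8% |

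At ρ = 0 there is no bias. If 4.2 is taken as the SD of change, 0.105 SD is 0.44 units; the article calls it only the SD in the maximum voluntary isometric contraction and gives no unit.

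If outside exercise were also applied during the trial, and removed the same share of controls whose exercise had improved them with the same correlation, the bias would double. At q = 20% and ρ = 0.3 that is 0.21 SD, with type I error √-formula SE of √(2/48) = 0.204 giving 17.7% at 0.05 and 3.8% at 0.005.

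**The case against.** The strongest reply is that the article names intention to treat as its governing principle and condenses a fuller document. The adherence criterion may describe withdrawal from the programme, or a secondary analysis set defined elsewhere. That is possible, and it is why the bias is stated here as conditional on the criterion being applied to the main comparison. It does not remove the conflict: the criterion stands in the eligibility list without any such limit.

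Three stronger readings are tempting, and the text does not support them.

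- A reader might infer that both criteria concern conduct after randomisation. That is certain only for low adherence. The words that place it during the programme attach to adherence, not to outside exercise. A screening bar on current exercise would not duplicate the one-year criterion, which covers only structured programmes.
- A reader might infer that adherence enters the model as a covariate, constant or undefined in controls and so confounded with group. The sentence is garbled, and the tests named (t-test, Mann-Whitney, χ², repeated measures analysis of variance, Friedman and Wilcoxon) include no covariate model. Adjustment for adherence is the most plausible meaning, but no specific model can be criticised.
- A reader might infer that every one of these features favours training. That direction is expected for dropping poor adherers. Removing training participants who also exercise elsewhere could work the other way, and no direction follows for an adjustment that is not specified.

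It is also fair that 5.1% to 23.5% applies only if 0.05 governs. The article also states 0.005, where the absolute rates are lower, although the relative inflation in the central case is larger.

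**Conclusion.** The point holds for low adherence: as written, the criterion removes randomised participants from the training arm alone and cannot be reconciled with the stated intention to treat. For outside exercise it holds only if the criterion is applied after randomisation, which the control-group monitoring suggests but does not establish. The adjustment phrase needs correcting whatever was meant, because it qualifies the only analysis principle given. If it means adjusting the main comparison for adherence, it conditions on a post-randomisation variable that controls do not have.

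The size cannot be derived from the article. Over assumed exclusions of 10% to 30% and correlations of 0.1 to 0.5, the bias from dropping poor adherers runs from negligible to a quarter of an SD. This should be fixed before analysis, because it decides who is analysed.

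**What to change.** - Remove low adherence from the exclusion criteria.
- State outside exercise as a baseline criterion only.
- Define the main analysis as all randomised participants in their allocated arm, and seek post-tests regardless of attendance.
- Delete the adherence adjustment from the main analysis.
- Report attendance descriptively as sessions attended out of 16 scheduled (8 weeks × 2), with one definition in place of the and/or wording.
- Put any adherence-based comparison in a labelled supplementary or per-protocol analysis, with its threshold set in advance.

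The cost is rewording in three short sections and some extra follow-up to obtain post-tests from people who stop attending. The estimate may be smaller, since it will include those who attended little. No new sample size follows from the change.

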### Randomisation and allocation

After baseline measurements, participants will be randomly assigned to the TG or CG. A research team member will create a randomisation sequence (1:1) before the trial begins. The investigators who will conduct the assessments are not aware of which group the participants belong to, and participants will be instructed not to disclose the group to which they had been assigned.

### Training group

The TG will perform circuit strength training with OFE in groups of six to eight people. Two sports science graduates will supervise the training programme, which will be carried out for 8 weeks, with two training sessions per week on non-consecutive days (table 1). To increase adherence, a third weekly session will be available for participants who could not attend on their schedule.

**Table 1 T1:** Progression in training during the study

Week	Workouts/week	Sets	Work/rest time (s)	Execution time (concentric-eccentric) (s)	Rest interval (s)
1	2	1	30/45	1–1	120
2	2	2	30/30	1–1	120
3	2	3	30/30	1–1	120
4	2	3	30/30	1–1	120
5	2	3	45/30	1–2	120
6	2	3	45/30	1–2	120
7	2	3	45/30	2–2	120
8	2	3	45/30	2–2	120

.s, seconds.

Over the 8 weeks, both the volume and intensity of the training will be progressively increased. Training load control considers variables such as time under tension, execution time, training density, rest between sets and total volume.

The session structure will be based on timed circuit training. Each session will specify work time, rest time, execution time and sets to perform (table 1). Work and rest times will be monitored through Timebirds Original V.3.12 (Melbourne, Australia). A mobile application metronome (Metronome Beats, UK) programmed at 60 beats per minute will indicate execution time with a series of beeps. Participants will perform repetitions constantly, using the metronome information to control execution time during the concentric and eccentric phases.

The warm-up will consist of aerobic exercises designed to elevate the heart rate (HR), which include 150 m of walking, increasing the walking speed every 50 m without transitioning to a run, 10 body weight squats and 10 standing push-ups against the wall. Following the aerobic exercises, participants will perform upper and lower joint mobility movements to prepare them for the training. The cool-down phase will involve gentle stretches of the major muscles targeted during the session, with 10 s of stretching per position. The training circuit will comprise 11 exercises conducted on 8 OFE from Entorno Urbano S.L.U (Murcia, Spain), installed at the university facilities. These machines offer different usage modes by varying grips and limb positions. Accordingly, the training circuit will be composed of the following machines in sequence: Bonny rider (the handle will be pulled using both hands with a supine grip, with the elbow being flexed and the shoulder being extended), Gemini Low Grip (the handle will be pushed with grips held at a low height, with the elbow being extended and the shoulder being flexed), Air Walker (hip flexion-extensions will be performed on both platforms with the torso being kept upright. A brief isometric hold will be done at the end of the motion), Parallel Bars (the body’s weight will be lifted by the elbow being extended from a flexed position. As an adaptation, triceps push-ups will be done sideways to the machine with a prone grip), Flyer Wheels circumductions (circumductions will be performed on the Flyers Wheels apparatus with elbows kept straight and grips being held, using shoulder mobility), Gemini Mid Grip (the handle will be pushed on the Gemini equipment with grips held at mid-level, by the elbow being extended and the shoulder being flexed), Flyer Wheels external rotation (internal and external rotations will be executed on the side of the Flyers Wheels machine, with the elbow being supported and the grip being held), Swing ankle extension (with the knee kept straight, the metatarsal will be rested on the platform’s lower edge and the ankle will be alternately flexed and extended), Surfboard (a pendulum motion from the waist will be done in the frontal plane while the handle is being held on the platform. An isometric hold will be performed at the motion’s furthest point), Swing leg press (resistance will be pushed against on the Swing apparatus with the knees being extended, while seated with feet on the platforms) and Row (on the seat, the movement will be performed by bending the elbow and shoulder, keeping the torso upright) (figure 2).

**Figure 2 F2:**
[figure not shown]
Images of the sequence and execution of the exercises on the different machines. (1) Bonny rider; (2) Gemini Low Grip; (3) Air Walker; (4) Parallel Bars; (5) Flyer Wheels circumduction; (6) Gemini Mid Grip; (7) Flyer Wheels External Rotation; (8) Swing Anke Extension; (9) Surfboard; (10) Swing Leg Extension; (11) Row.

Each machine will be numbered with a sign to indicate the execution order to the participants (figure 3), allowing for alternating work on different muscle groups to prevent excessive localised fatigue. The starting exercise for each participant and session will be randomised to avoid potential influences on ratings of perceived exertion (RPE) and HR. The initial machine will be recorded for each participant in each session.

**Figure 3 F3:**
[figure not shown]
Images of flashcards indicating the sequence of use for the outdoor fitness equipment during the training programme.

At the session’s end, data on HR will be collected using a wrist-worn HR monitor, the Polar M430 (Polar Electro, Kempele, Finland), and participants’ RPE after each exercise and at the end of the session will be recorded. Potential exercise adaptations will be based on participants’ functional and physical capacity, assessed by an expert committee and considering the machines’ everyday use.^12^

### Control group

Individuals assigned to the CG (figure 1) will be instructed to continue their daily activities throughout the study. Participants’ habits and physical activity levels will be monitored over the 8-week study period using specific inquiries incorporated within the socio-demographic questionnaire.

### Data collection and measures

Measurements will be performed in the laboratory of the research group available at the university. Participants will be asked not to stretch or warm up before the tests. Measurers will be maintained from pre-test to post-test to avoid the influence of inter-rater error on the measurements made. Experts in the performance of the specified tests will evaluate all measurements. The tests will be performed in a random order. Variables collected and the assessment schedule during the study are shown in table 2.

**Table 2 T2:** Variables were collected, and assessments were scheduled during the study

	Training group			Control group		
	Baseline	Intervention	Post	Baseline	Intervention	Post
Consent	X			X		
Demographic survey: Age, sex, occupation, weekly physical activity, pathologies and medication	X			X		
Health-related quality of life: 36-Item Short Form Survey	X		X	X		X
Satisfaction with life: Satisfaction with Life Scale	X		X	X		X
Adherence to the Mediterranean diet: Prevention of Mediterranean Diet Score	X		X	X		X
Body composition: Height and weight Full body composition (DEXA) Bone mineral density (DEXA)	X		X	X		X
Blood pressure	X		X	X		X
Heart electrical activity: ECG	X			X		
Muscular strength: Isometric handgrip strength test Isometric knee extension strength test Isometric elbow flexion strength test	X		X	X		X
Cardiovascular fitness: 400 metres walking test	X		X	X		X
Postural stability: Centre of pressure (COP) in side-by-side test Centre of pressure (COP) in semi tandem test Centre of pressure (COP) in tandem test	X		X	X		X
Functional capacity: Short physical performance battery (SPPB) Time Up and Go Test	X		X	X		X
Risk of falls: Gait speed test	X		X	X		X
Risk of sarcopenia: European Working Group on Sarcopenia in Older People Consensus	X		X	X		X
Sagittal spine disposition and pelvic tilt: Spinal mouse relaxed standing position test Spinal mouse relaxed sitting position test	X		X	X		X
Rating of perceived exertion: 1–10 Borg rating of perceived exertion		X				
Effort and heart rate		X				
Training volume		X				
Adherence		X				

DEXA, dual-energy X-ray absorptiometry.

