### Primary outcomes

#### Maximum muscular strength

Both maximum knee extension and elbow flexion strengths will be evaluated under the same isometric conditions. For the knee extension test, participants will be seated in a chair specifically designed for the measurement of isometric knee extension strength (ES-1295254) equipped with a force transducer (Musclelab, Ergotest, Norway), maintaining both a hip and knee angle at 90 degrees. Participants will be directed to exert maximum strength against a pad above their ankle joint. For the elbow flexion test, participants will stand upright, holding a bar with both hands in a supine position, with the elbow at a 90-degree angle. Participants will be directed to exert maximal strength against the bar.

Following a previous protocol, participants will sustain exertion for 2–3 s during both assessments.^13^ The software (Musclelab, Ergotest, Norway) will quantify the maximum voluntary isometric contraction and the rate of force development. Each participant will complete three trials for each assessment, and the best one will be used.

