#### Cardiorespiratory fitness

The 400 m walking examination is deemed a suitable and reliable test for approximating cardiorespiratory fitness (CRF).^14^ So CRF will be evaluated by measuring the time needed to complete 10 laps as rapidly as feasible on a 20 m long track. Participants will be directed to walk at their maximum pace, refraining from running.^14^ The maximum and average HR during the test will be evaluated, and the HR with the test will be finished. Also, the HR 2 min after the test will be recorded as the CRF recovery variable. A single attempt at the test will be done.

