#### Postural stability

A force platform will assess postural stability during quiet standing (Musclelab, Ergotest, Norway). The short physical performance battery (SPPB) balance protocol will be followed.^15^ Participants will be maintaining a stationary stance for 30 s with arms at their sides, repeated three times in each foot position, following this order: (1) feet together with eyes open; (2) semi-tandem stance (one foot’s ankle behind the joint of the other foot) with eyes open; and (3) tandem stance (one foot’s ankle directly behind and touching the other foot’s ankle) with eyes open. Measurements such as the total centre of pressure displacement, anteroposterior and mediolateral amplitudes of the centre of pressure and the area of the centre of pressure displacement will be obtained from analyses conducted with Musclelab software (Musclelab, Ergotest, Norway).

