#### Blood pressure

Blood pressure will be measured using an automatic blood pressure monitor (OMRON model HEM-7113, Osaka, Japan), following the general guidelines.^23^ The participant will sit comfortably and quietly for 5 min before the first measurement, with the second measurement taken 2 min later. The final values of systolic blood pressure, diastolic blood pressure and pulse rate were the average of the two measurements. Subjects will be informed to abstain from vigorous exercise for 24 hours, avoid caffeine intake for 4 hours and refrain from tobacco use 30 min before the measurements.

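### Tests are run in random order with no exemption for resting measures, so blood pressure and pulse may be read after maximal efforts, in tension with the article's own 24-hour abstention rule

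*Protocol article*

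**What the plan says.** The rule on order is in Data collection and measures: "The tests will be performed in a random order". The same paragraph keeps the measurer constant from pre-test to post-test and adds "Participants will be asked not to stretch or warm up before the tests". It does not say whether order is drawn once per participant or again at each visit. Table 2, which follows, lists blood pressure, DEXA and relaxed spinal posture at baseline and post, together with the isometric strength tests, the 400 m walk and the functional tests.

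Under Blood pressure, which also yields pulse rate, the preparation rule is "Subjects will be informed to abstain from vigorous exercise for 24 hours". On the day, "The participant will sit comfortably and quietly for 5 min before the first measurement", with a second reading 2 min later and the two averaged.

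Two sections describe hard efforts. Cardiorespiratory fitness has "Participants will be directed to walk at their maximum pace, refraining from running". Maximum muscular strength, which covers knee extension and elbow flexion, has "Each participant will complete three trials for each assessment, and the best one will be used".

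A sequence is set in two places only. Inclusion and exclusion procedures puts the ECG "just after signing the informed consent and before the assessment tests", and Postural stability has the stances "repeated three times in each foot position, following this order".

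**The concern.** Read literally, the order rule can supply the very exertion that the blood pressure section asks participants to avoid. A participant may be drawn to walk 400 m as fast as possible, or to make repeated maximal contractions, and then have blood pressure and pulse taken after a few minutes of sitting. Relaxed spinal posture might be affected in the same way.

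A second consequence is conditional. The main comparison is of change from baseline to follow-up. If a participant's order differs between the two visits, any fatigue or carry-over differs too and enters the change score as noise. Blood pressure is a secondary outcome. Strength, postural stability and the 400 m walk are listed as primary, and they are sensitive to preceding effort. The article accepts the principle elsewhere: it keeps measurers constant, and in the Training group section it randomises the starting machine and records it for each participant and session.

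**Working it through.** The article gives no figure on this point, so none has to be reproduced. Two stated values serve only as a scale: 60 per group and 95% power (the sample-size paragraph under Ethics approval and dissemination). A two-sided 0.05 level is assumed, because sidedness is not stated.

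**1. Does blood pressure fall under the order rule?**
- The rule refers to the tests without qualification.
- The Body composition section calls the DEXA scan a test, and Table 2 calls the Spinal Mouse positions tests. The word is therefore not reserved for physical efforts.
- The ECG and the stances have a stated sequence. Blood pressure has none.

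The broad reading is natural, though not the only possible one.

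**2. How often would blood pressure follow an effort?** Assume that blood pressure is in the random order, that all orders are equally likely, and that all tests share one visit.
- After the 400 m walk: 1/2 = 50%.
- After at least one of m effort tests: 1 − 1/(m+1) = m/(m+1).
- m = 4 (knee extension, elbow flexion, handgrip, 400 m walk): 4/5 = 80%.
- m = 8 (adding chair stand, Timed Up and Go, and the 10 m and 4 m walks): 8/9 = 89%.

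Not every one of these need count as vigorous exercise. The 400 m walk is the clearest case, so 50% is the safer figure.

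**3. What would a redrawn order add to the change score?** Assume independent draws at the two visits and a constant shift of c standard deviations of the change score whenever the effort comes first.
- Let the indicator be 1 if the effort comes first. Its variance at each visit is 0.5 × 0.5 = 0.25.
- The difference of two independent indicators has variance 0.25 + 0.25 = 0.5, and the indicators disagree in 50% of participants.
- Added variance, relative to the change score: 0.5 × c² = c²/2.
- Equivalent sample size: 60/(1 + c²/2).
- Power, starting from 95%: Φ[(1.960 + 1.645)/√(1 + c²/2) − 1.960].

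| c (assumed) | Added variance | 60 per group acts like | Power from 95% |
|---|---|---|---|
| 0.10 | 0.5% | 59.7 | 94.9% |
| 0.25 | 3.1% | 58.2 | 94.4% |
| 0.50 | 12.5% | 53.3 | 92.5% |
| 1.00 | 50% | 40.0 | 83.7% |

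As an illustration in blood pressure units, with an assumed SD of change of 10 mmHg, a shift of 5 mmHg is c = 0.5 and adds 12.5%.

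**4. What if each participant keeps one order?** The two indicators are then equal, their difference is zero, and a constant shift adds nothing to the change score. A resting reading taken after effort would still not be a resting reading.

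**The case against.** The strongest reply is that the conflict needs two things the article does not state: that blood pressure is one of the tests, and that it shares a visit with the effort tests. The blood pressure section speaks of measurement rather than testing. The 24-hour rule stands beside those on caffeine and tobacco and can be read as preparation before attendance. The section also has its own safeguards: quiet sitting and two averaged readings. Random order is a recognised way to avoid loading fatigue on the same tests, and a journal article may leave scheduling detail to the full protocol.

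Much of this stands. It makes the point a tension under the natural reading of a stated rule, not a proven contradiction. It does not remove the point, because the rule is stated without exception and followed literally it allows the sequence described.

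A reader might go further in five ways that the document does not support:
- **That every test is in random order.** The ECG comes first and the stance order is fixed.
- **That every change score gains noise.** Questionnaires, height and bone density have no evident order effect.
- **That the post-test order does differ.** The article is silent, so this is only a possibility.
- **That resting blood pressure is invalidated.** The size of any shift is unknown, and the seated rest protects in part.
- **That random order defeats the no-warm-up instruction.** That instruction concerns what participants do before the tests, and under any sequence later tests follow earlier ones.

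**Conclusion.** The point holds in a limited form. The order rule does not exempt resting measures. If assessments share a visit, blood pressure and pulse rate, and possibly relaxed spinal posture, can be taken after maximal efforts, in tension with the abstention rule. On the assumptions in step 2, this concerns half of visits for the 400 m walk alone.

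Random order applied alike in both arms does not bias the comparison between them. The cost is compromised resting readings and, only if order is redrawn at post-test, extra variance in the change of effort-sensitive outcomes. That variance is small for modest carry-over (about 3% at c = 0.25) and noticeable at 12.5% for c = 0.5. Nothing in the document fixes c, so the table is a range and not an estimate. No figure stated in the article is wrong because of this point.

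**What to change.** Reconcile Data collection and measures with Blood pressure:
- State that the resting measures (blood pressure with pulse rate, spinal posture, DEXA) precede all effort tests.
- Limit random order to the physical performance tests.
- Record each participant's baseline order and repeat it at post-test.

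The Introduction describes the trial as ongoing. Participants already tested at baseline should therefore repeat their own baseline order where it is known, since imposing a new sequence on them would itself create a difference between visits. The cost is slightly less flexibility in scheduling the testing day; sample size, outcomes and analysis are unchanged.
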